### 2.2 Objectives

#### 2.2.1 Primary Objective

- To determine if daclizumab inhibits the functional and numeric recovery of TRegs after therapeutic TMZ-induced lymphopenia in

---

 TTP, time to progression

the context of vaccinating adult patients with newly-diagnosed high grade gliomas using CDX-110.

### **2.2.2      Secondary Objectives**

- To evaluate the safety of daclizumab in the context of vaccinating adult patients with newly-diagnosed high grade gliomas using CDX-110 during recovery from therapeutic TMZ-induced lymphopenia.
- To determine if daclizumab enhances the magnitude or character of CDX-110-induced cellular or humoral immune responses, inhibits or enhances activation-induced cell death, or induces immunologic or clinical evidence of autoimmunity.
- To determine if daclizumab alters the phenotype (CD56-expression), cytokine secretion profile, or cytotoxicity of CD3-CD56+ NK cells.
- To determine if daclizumab in addition to vaccination extends progression free survival compared to historical cohorts.
- To characterize immunologic cell infiltrate in recurrent tumors and seek evidence of antigen escape outgrowth.

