## 2 HYPOTHESES AND OBJECTIVES

### 2.1 Hypotheses

- Our primary hypothesis is that:
  - Daclizumab will inhibit the functional and quantitative recovery of TRegs in patients with newly-diagnosed high grade glioma during homeostatic proliferation after therapeutic TMZ-induced lymphopenia.
- Secondary hypotheses that will be explored in this study are that:
  - Daclizumab will be safe in combination with CDX-110 in patients with newly-diagnosed high grade glioma during recovery from TMZ-induced lymphopenia.
  - The magnitude and character of humoral and cellular CD8+ and CD4+, EGFRvIII-specific T cell responses will be enhanced in adult patients with newly-diagnosed high grade glioma treated during recovery from TMZ-induced lymphopenia when daclizumab is given during the T cell recovery phase.
  - Daclizumab will not enhance antigen-specific or generalized activation-induced cell death or induce immunologic or clinical evidence of autoimmunity.
  - Daclizumab will alter the phenotype (CD56-expression), cytokine secretion profile, or cytotoxicity of CD3-CD56+ NK cells.
  - Treatment of adult patients with newly-diagnosed high grade glioma using CDX-110 during recovery from TMZ-induced lymphopenia with or without daclizumab will ultimately produce evidence of a prolonged time to progression (TTP) and overall increase in median survival in these patients compared to a matched historical cohort from MD Anderson Cancer Center (provided by [name]).

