site reactions with urticaria, while one patient experienced mild fever thought possibly related to PEP3-KLH. A single patient experienced radiographic changes suggestive of focal demyelination in the pons and corpus collosum after an eleventh vaccination but remained entirely asymptomatic. The radiographic abnormalities improved spontaneously despite continued vaccination. Another patient was reported to have a grade 3 allergic reaction following vaccination, but had a similar experience in association with an MRI study – both consistent with an anxiety process. The investigator discontinued vaccination in this patient despite the patient's desire to continue.

Delayed-type hypersensitivity (DTH) testing showed no response to components of PEP-3-KLH at baseline, but at 6 months, 62% of patients were immunologically reactive to at least one component of the vaccine. The vaccination induced a statistically significant increase in PEP3-specific  $\gamma$ -IFN producing T cells, and increased EGFRvIII-specific antibody titers that correlated with time to tumor progression (TTP). Overall, 38% of the vaccine patients produced EGFRvIII specific humoral immune responses that were at least five-fold greater than pre-vaccine levels (p=0.0008).

Median TTP in the vaccine-treated patients was 12.1 months, comparing favorably with a matched, unvaccinated historical cohort of thirty-nine (39) patients treated at MD Anderson (7.1 months; p=0.0058), and with those obtained using the accepted standard of care of concurrent temozolomide and radiation followed by adjuvant temozolomide (6.9 months) (Cohen, Johnson et al. 2005; Stupp, Mason et al. 2005). Final median survival has not been reached at median follow-up of 19 months, which again compares favorably with the matched historical cohort (13 months) and the standard of care therapy group (14.6 months). Six (6) patients experienced recurrence of GBM and were evaluated by immunohistochemistry. Of these, none were found to maintain expression of EGFRvIII,

consistent with elimination of EGFRvIII expressing cells, or loss of expression of the EGFRvIII antigen.

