### **7.3 Time to Progression (TTP)**

Patients potentially eligible for this study will be followed from the time of their initial presentation, if possible. The TTP will be defined radiographically or clinically, as delineated above; or alternatively defined by a significant overall change in clinical status as assessed by the study neuro-oncologist, [name]. or his designate. In the absence of radiographic or histologic evidence of progression, clinical progression will be defined as a change in KPS of  $>30$  points or a change in MMSE of  $>6$  points that is not reversible with medical therapy within 2 months. Clinical progression in this context will constitute a DLT if not attributable to a concomitant medication, co-morbid event, or disease progression that has been documented radiographically or clinically.

An intent-to-treat analysis will be conducted to compare the TTP experience of patients identified to receive vaccine treatment upon completion of concurrent external beam radiation and temozolomide assuming there was no intervening disease progression to that experienced by a historical cohort of patients administered the same external beam radiation and temozolomide treatments(Stupp, Mason et al. 2005). Of particular interest is whether the TTP experience of the two groups begins to diverge at the time that vaccine is administered 3-4 months after patient enrollment.

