1972) will be used to compare TTP and survival between the groups and with appropriate matched historical control groups. We would consider daclizumab worthy of further evaluation only if it did not significantly reduce TTP or overall survival relative to the control group and relative to the historical controls. Therefore, in the proposed study, we are interested in determining whether either treatment regimen is definitely worse than our best contemporaneous results at Duke University which are with the use of radiolabeled MABs delivered intratumorally. The most recent Phase II trial evaluating radiolabeled MABs at Duke in patients with newly-diagnosed GBM had a median survival of 79.4 weeks, and the lower limit of the 95% confidence interval was 61.4 weeks. Assuming that survival is exponential in this context, a median of 61.4 weeks translates into a 6-month survival of approximately 75%. Therefore if 6-month survival is not definitively <75%, there would remain interest in further development of the regimen proposed here. With 10 patients in each arm of our trial, one can conduct a test with  $\alpha=\beta=0.1$  to differentiate between a 6-month survival rate of 35% and 75%. That means that if the true 6-month survival rate were  $\leq 35\%$  there is <10% chance of concluding that the treatment regimen is worthy of pursuing with further investigation. Similarly, if the true 6-month survival rate were  $\geq 75\%$  or more there is  $\leq 10\%$  chance of rejecting the treatment. Other comparison groups that could be used include a historical control database, the recently published Phase III trial of the regimen of TMZ to be used in this trial, or our previous trial dataset using this vaccine approach which had median survivals (95% CI) of 14.7 (12.0, 17.4), 14.6 (10.9, 21.2), and >29.8 months, respectively. In addition, we will assess clinical efficacy by estimating the proportion of patients who survived longer than expected according to Curran's recursive partition analysis (Curran, Scott et al. 1993).

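### Secondary objective 4 asks what daclizumab adds to vaccination but names only historical cohorts, and a comparison with those cohorts cannot separate daclizumab from the vaccine

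*Protocol*

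**What the plan says.** Section 2.2.2 gives the objective: "To determine if daclizumab in addition to vaccination extends progression free survival compared to historical cohorts". The synopsis repeats it. Neither place says which cohorts are meant or whether they were vaccinated.

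Four other sections bear on it:

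- **Section 2.1.** The matching hypothesis is that the vaccine "with or without daclizumab will ultimately produce evidence of a prolonged time to progression" and longer median survival, "compared to a matched historical cohort from MD Anderson Cancer Center".
- **Section 7.3.** An intent-to-treat analysis will "compare the TTP experience of patients identified to receive vaccine treatment upon completion of concurrent external beam radiation and temozolomide" with a published cohort treated with the same radiation and temozolomide.
- **Section 3.4.3.** On the earlier vaccine trial, which did not use daclizumab: "Median TTP in the vaccine-treated patients was 12.1 months, comparing favorably with a matched, unvaccinated historical cohort". That cohort had 39 patients, was treated at MD Anderson and had a median TTP of 7.1 months. The figure for standard radiation plus temozolomide is 6.9 months.
- **Section 10.3.** A Cox model will compare TTP between the two randomised groups and also with matched historical controls. The section then adds "Other comparison groups that could be used include a historical control database". The list that follows includes the previous vaccine trial, with a survival figure but no TTP.

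Section 5.1.1 randomises cohort 1 to daclizumab or saline at the first vaccination. Cohort 2 (6 patients) all receive serial daclizumab, without a randomised control.

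**The concern.** To learn what daclizumab adds to vaccination, the comparator must also have been vaccinated. The objective offers only history. The two cohorts identified for TTP are the matched MD Anderson cohort, described as unvaccinated in section 3.4.3, and radiation-plus-temozolomide patients. Set against either, the daclizumab arm differs by the vaccine as well as by daclizumab.

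By the protocol's own account the vaccine alone is associated with about five extra months of median TTP. A daclizumab with no effect could therefore look beneficial if results were reported against this objective as worded. The trial already has the right control, the randomised vaccine-plus-saline arm, but the objective does not refer to it.

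**Working it through.** The protocol attaches no sample size, significance level or threshold to this objective, so there is no planned figure to reproduce. The check first compares the passages, then sizes the vaccine effect that the historical comparison would carry.

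**1. What each passage compares**

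| Place | Patients assessed | Comparator | Can isolate daclizumab? |
|---|---|---|---|
| 2.2.2, objective 4 | Daclizumab plus vaccine | Historical, unspecified | Not with the cohorts identified for TTP |
| 2.1 | Vaccinated, either arm | Matched MD Anderson cohort | No |
| 7.3 | All identified to receive vaccine | Radiation plus temozolomide | No |
| 10.3, Cox between groups | Vaccine plus daclizumab | Vaccine plus saline (randomised) | Yes |

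Only the last row answers the question in objective 4, and section 10.3 does not link it to that objective.

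**2. Apparent effect of an inert daclizumab**

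Inputs from section 3.4.3: median TTP 12.1 months with vaccine and no daclizumab; 7.1 months in the matched cohort of 39; 6.9 months with standard care.

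- Difference in medians: 12.1 − 7.1 = 5.0 months; 12.1 − 6.9 = 5.2 months.
- Hazard ratio if TTP is exponential (inverse ratio of medians): 7.1/12.1 = 0.587; 6.9/12.1 = 0.570.

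**3. Chance of a nominally significant extension with 10 daclizumab patients**

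Assumptions: daclizumab has no effect, the vaccine performs as before, TTP is exponential, and all patients have progressed (10 events; 39 in the matched cohort). The significance levels are mine. Two-sided results use 0.025 in the favourable tail.

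*Fixed 6.9-month median.* Under the null, twice the total time divided by the reference mean is chi-square on 2 × 10 = 20 degrees of freedom. The rejection probability is P(χ²₂₀ > critical value × 0.570).

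- One-sided 0.05: critical value 31.41; 31.41 × 0.5702 = 17.91; probability 0.59.
- Two-sided 0.05: critical value 34.17; 34.17 × 0.5702 = 19.49; probability 0.49.

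*Matched cohort of 39 at 7.1 months.* The ratio of mean times is F on 20 and 78 degrees of freedom. The rejection probability is P(F > critical value × 0.587).

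- One-sided 0.05: critical value 1.707; 1.707 × 0.5868 = 1.001; probability 0.47.
- Two-sided 0.05: critical value 1.889; 1.889 × 0.5868 = 1.108; probability 0.36.

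A log-rank approximation (Schoenfeld) for 10 against 39 gives slightly lower values, 0.44 one-sided and 0.32 two-sided. The nominal rate is 0.05.

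**4. What the randomised contrast can do**

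If daclizumab is inert, the expected hazard ratio between the randomised arms is 1, so the vaccine effect cancels. With 10 per arm and all 20 progressed, 80% power requires a hazard ratio of exp[−2(1.960 + 0.842)/√20] = 0.29 (two-sided 0.05), or exp[−2(1.645 + 0.842)/√20] = 0.33 (one-sided). The contrast is free of the vaccine effect but can only be descriptive.

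**The case against.** Much can be said for the protocol.

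- **The right comparison is already planned.** Section 10.3 has Kaplan-Meier curves by treatment group and a between-group Cox comparison of TTP. It judges daclizumab worth pursuing only if TTP and survival are not significantly worse than in the control arm and in historical controls. This stands. But it is a no-harm rule, whereas objective 4 asks whether daclizumab extends progression-free survival.
- **The historical comparison is framed elsewhere as one of the regimen.** Sections 2.1 and 7.3 concern vaccinated patients whatever their daclizumab assignment. This also stands, and it shows that objective 4 is the text out of line.
- **The objective does not call its cohorts unvaccinated.** Correct. That is inferred from sections 2.1, 3.4.3 and 7.3, and section 10.3 mentions the earlier vaccine dataset as a possible comparator. The inference is direct for the cohorts identified for TTP.
- **The endpoint is exploratory.** Section 10.3 makes TTP hypothesis-generating, and section 8.1.1 says the same of every non-primary analysis. This limits the consequence.

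A reader might infer that the vaccine's effect will be reported as a daclizumab effect, or that the objective can be declared met when the drug does nothing. The documents support neither. The randomised comparison is planned, and the objective carries no test or success threshold. Nor should the probability be computed on all 20 cohort 1 patients and read as a false-positive rate for daclizumab. Half of them receive saline, so that figure would be power for the vaccine hypothesis in section 2.1.

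**Conclusion.** The concern holds as a misaligned objective. Read with the cohorts identified for TTP, objective 4 names a comparator that cannot separate daclizumab from the vaccine, and it disagrees with sections 2.1, 7.3 and 10.3. It does not hold as a charge that the plan lacks a vaccinated control.

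The vaccine effect carried into the historical comparison is a hazard ratio of 0.57 to 0.59. For 10 patients on an inert daclizumab, that means a nominally significant result with probability 0.47 to 0.59 one-sided, or 0.36 to 0.49 two-sided. These figures rest on exponential TTP, complete progression and the earlier 12.1-month median carrying over. The last is uncertain: the earlier trial enrolled glioblastoma after gross-total resection, while this one admits WHO Grade III tumours and provides for residual disease. The structural point does not depend on the exact figures. It applies most fully to cohort 2, which has no randomised control. The consequence is modest because the endpoint is exploratory.

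**What to change.** 1. Reword objective 4 in section 2.2.2 and the synopsis. The effect of daclizumab on TTP or progression-free survival is the randomised cohort 1 contrast, vaccine plus daclizumab against vaccine plus saline. It is estimated with the Cox model already in section 10.3 and reported descriptively as a hazard ratio with its confidence interval.
2. In section 7.3, label the historical comparison as one of the vaccine-temozolomide regimen, whichever daclizumab assignment patients had. State that no claim about daclizumab is drawn from it, including for cohort 2.
3. Add to section 10.3 a cross-reference from the between-group Cox comparison to objective 4.

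The cost is a few sentences, with no new patients, data or model. The sponsor gives up a historical claim about daclizumab and is left with an imprecise randomised estimate. The endpoint remains exploratory.

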## **3 BACKGROUND AND RATIONALE**

### **3.1 Disease and Current Therapy**

Malignant primary brain tumors are more common than Hodgkin's disease and account for more human deaths than melanoma or than cancer of the bladder or kidney. Despite aggressive, computer-guided tumor resection(Kelly 1992), high-dose external beam RT or brachytherapy, and multi-mechanistic chemotherapy delivered at toxic doses, most patients with malignant primary brain tumors live <15 months from the time of diagnosis, and patients with recurrent tumors usually survive <12 weeks(Walker, Alexander et al. 1978; Walker, Green et al. 1980; Shapiro 1986; Salford, Brun et al. 1988; Dinapoli, Brown et al. 1993; Stupp, Mason et al. 2005). The estimated cost of treatment for each patient with a malignant brain tumor is between \$30,000 and several hundred thousand dollars annually. Thus, the annual treatment cost alone for these patients, not mentioning the lost earning potential of afflicted individuals, is greater than the entire annual budget of the National Institute of Neurological Diseases and Stroke. In fact, conventional therapy for patients with malignant brain tumor is the most expensive medical therapy per quality-adjusted life-year saved currently provided in the United States(Pickard, Bailey et al. 1990; Ekman and Westphal 2005). Moreover, the non-specific nature of conventional therapy for brain tumors often results in incapacitating damage to surrounding normal brain and systemic tissues(Imperato, Paleologos et al. 1990; Hall and Fodstad 1992). Thus, in order to be more effective, therapeutic strategies will have to precisely target tumor cells while minimizing collateral damage to neighboring eloquent cerebral cortex. The rationale for employing the immune system to target brain tumors is based on the premise that the inherent biologic specificity of immunologic reactivity could meet the clear need for more specific and precise therapy.

### **3.2 Vaccine Therapy for Cancer**

There is extensive precedent for using therapeutic vaccines to target tumor specific or tumor relevant antigens. Many different vaccine constructs have been combined with different antigens and given via differing routes and doses with limited success at achieving tumor control. While no optimal vaccine formulation has been defined, essentially due to the lack of documented clinical efficacy with which to characterize an optimal formulation, it is clear that intradermal administration is an effective way to present antigens to the immune system, and assorted immunologically active molecules can be used to augment the immunogenicity of the vaccine.

Adjuvants frequently used with vaccination include Freund's incomplete adjuvant, bacilli Calmette-Guerin, QS-21, and diphtheria toxoid. Supplemental cytokines have been used as well for the adjuvant immunological effects (Rosenberg, Yang et al. 1998). Granulocyte macrophage-colony stimulating factor (GM-CSF) has been commonly used, as it is commercially available and well tolerated. GM-CSF is capable of stimulating macrophage function, inducing proliferation and maturation of dendritic cells, and is able to enhance T-lymphocyte stimulatory function. Intradermal administration of GM-CSF enhances the immunization efficacy at the site of administration in a dose dependent

fashion at an optimal dose of 125 µg (Kremer, Stevens et al. 2000). Significant anti-tumor immunity has been demonstrated in preclinical murine studies in which irradiated, stably transfected tumor cell lines secreting GM-CSF have protected against subsequent tumor challenge, especially against intracerebral tumors ([name], Ashley et al. 1997; Mach, Gillessen et al. 2000). Furthermore, the potency of GM-CSF has been demonstrated in a Phase I clinical trial in melanoma patients vaccinated with irradiated autologous melanoma cells engineered to secrete GM-CSF (Soiffer, Lynch et al. 1998). The immunization sites were intensely infiltrated with T lymphocytes, dendritic cells, macrophages, and eosinophils in 100% of evaluable patients. Extensive tumor destruction was seen in 11 of 16 patients. Both cytotoxic T cells and antibody responses were associated with this tumor destruction. Hence, GM-CSF has an extensive track record both as a growth factor and an adjuvant, is commercially available and has an acceptable toxicity profile. The experience on the ACTIVATE study supports the use of GM-CSF and sets the precedent for this phase II/III study.

### **3.2.1 CNS Immunologic Privilege**

The CNS is an immune privileged site. Clearly, however, in situations where a CNS antigen has generated a strong immune response (Multiple Sclerosis or encephalitis) or in situations where the Blood Brain Barrier has been disrupted, it is quite possible to develop potent immune activity within CNS tissues. In the post-operative setting, where the CNS immune isolation is compromised, it is likely that an effective immune response could eliminate targeted malignant cells. Considering that an acutely ruptured Blood Brain Barrier could be revealing an area to which a patient's immune system has had only limited exposure, it is conceivable that this could be an ideal setting to generate de novo immune responses in the absence of pre-existing immune regulatory elements. The preclinical data in EGFRvIII expressing xenotransplant animal models, and the human experience with EGFRvIII vaccination to date, are consistent with effective immune control of CNS malignancy.

Experience to date in vaccinating patients against antigens expressed within the CNS has been very limited. Several other vaccine approaches against CNS tumors are in development, but no definitive data supporting this approach has been published.

### **3.2.2 Immunotherapy and Chemotherapy Combination**

Cancer vaccines can elicit tumor-reactive humoral and cellular immune responses. To date, these responses have not reliably been able to eliminate tumor, potentially due to the multiple immune suppressive mechanism present within the malignant environment. While it has been traditionally felt that chemotherapy would compromise the cellular elements necessary to generate immune responses, recent data suggest that perhaps chemotherapy can augment immune effects through either preferential elimination of regulatory components, or amplification of antigen exposure following cytotoxic cell damage (Emens, Machiels et al. 2001; Machiels, Reilly et al. 2001; Wheeler, Das et al. 2004; Chong and Morse 2005; Emens and Jaffee 2005; van der Most, Currie et al. 2006). In general, it appears that the immune system regenerating from a cytotoxic insult may be hyperacutely activated and particularly responsive due both to increased stimulatory cytokines within the environment and reduced regulatory elements. This protocol will give vaccination during the recovery phase of each maintenance chemotherapy cycle (day

21 of 28), allowing approximately 1 week for the immune activation prior to the initiation of the next cycle of temozolomide. (See IB for lymphocyte recovery data)

